#### Methodology

Patients will be remunerated $20 with a gift card after completing a baseline survey. Most surveys will be completed online by the study participants directly or over the phone with a trained interviewer. Any mailed surveys will be returned to KPSC and entered into the study’s assessment database. A double-data entry method will be used to ensure accurate data entry. Separate databases will be created for each patient’s registration/contact information and assessment data. Each patient will be given a unique, arbitrary study identification number that can be used to associate their contact and registration information and assessment data. Once the 1200 surveys have been collected and entered, this data will be analyzed to determine baseline differences in transplant knowledge, informed decision-making, self-efficacy, and steps toward transplant between patients varying in race/ethnicity, primary language, and CKD stage before patients are given an intervention.

### Evaluation and statistical analysis plan

#### Power analysis

Based on the following assumptions, we estimated the sample size for the RCT. Using data from previous RCTs [4, 35], a mean knowledge change score of 1.0 points is estimated necessary to be detected among patients receiving *ET@Home* and standard KPSC education. Patients’ baseline transplant knowledge scores will be correlated with those of other patients from the same clinics [intraclass correlation coefficient (ICC) of 0.31]. The variance in knowledge change has both between- and within-cluster components, yielding a pooled standard deviation estimate of 4.0. Participant retention will be 50% at the 6-month assessment. Outcomes will be assessed using two-tailed statistical tests. Type 1 error rate (alpha level) will be set at 0.05. This study design will ensure power of 0.90. Power calculations for this trial are based on all of these factors, which yields a standardized effect size, accounting for clustering of approximately 0.257.

Power analyses based on changes in transplant knowledge, our primary study outcome, are presented. The study design and analyses were treated as a test of the difference between the mean knowledge score change of CKD patients in the *ET@Home* and standard KPSC education (control) conditions six months post-baseline. It is estimated that with 600 completed surveys (50% attrition), there will be a 90% power to detect a 0.25 effect size between two equal-sized groups (control and treatment groups). By stratifying recruitment and randomization by race/ethnicity (Asian, Black, Hispanic, White), primary language spoken (English vs. Spanish), and stage of CKD, according to the table below, this sample size will also have 90% power to detect 1 point differences in change on the transplant knowledge scale between the *ET@Home* and standard KPSC education conditions for these critical subgroups using interaction terms (e.g., treatment by race interaction, language by race interaction). Patients enrolled and randomized are shown in Table 3.

**Table 3 Tab3:** Patients enrolled and randomized

Race/Ethnicity/Language	Stage of CKD			
	3^a^	4	5/ESRD	Total
*English-speaking Asian*	67	67	66	200
*English-speaking Black*	67	66	67	200
*English-speaking White*	67	67	67	200
*English-speaking Hispanic*	67	67	66	200
*Spanish-speaking Hispanic*	133	133	134	400
Total	400	400	400	1200

^a^
*CKD* 3 patient recruitment prioritized based on likelihood to progress

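### The stated 90% power does not follow from the printed inputs: 600 completers give about 86% at an effect of 0.25 and 88% at 0.257, and the two effect sizes are not reconciled

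*Protocol article*

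**What the plan says.** All the inputs are in the Power analysis section of the protocol article.

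- Target difference: "a mean knowledge change score of 1.0 points is estimated necessary to be detected".
- Variability of the powered outcome: "The variance in knowledge change has both between- and within-cluster components, yielding a pooled standard deviation estimate of 4.0".
- Test: "Outcomes will be assessed using two-tailed statistical tests", and "Type 1 error rate (alpha level) will be set at 0.05".
- Stated power: "This study design will ensure power of 0.90".
- Effect size in the first paragraph: the listed factors together are said to give a power calculation "which yields a standardized effect size, accounting for clustering of approximately 0.257".
- Effect size in the second paragraph: "with 600 completed surveys (50% attrition), there will be a 90% power to detect a 0.25 effect size between two equal-sized groups".

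The section also gives an intraclass correlation of 0.31, assigned to baseline knowledge scores within clinics, and 50% retention at six months. Elsewhere the article describes 1:1 randomisation of individual participants (Study participants section), 600 patients per condition (Outcome measures section), and a multilevel model for change scores with a random clinic intercept (Statistical analysis section).

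**The concern.** The second paragraph makes a complete power statement: number of completers, effect size, equal groups, and the test fixed just above it. It can therefore be checked directly, and 600 completers look too few for 90% power at an effect of 0.25.

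The section also carries two effect sizes. The target of 1.0 point over an SD of 4.0 is exactly 0.25, yet the first paragraph reports 0.257 after allowing for clustering. The only ICC printed describes a different variable (the baseline score) from the one being powered (the change score), so a reader cannot see how 0.257 arose or which effect the 90% refers to.

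This is the article's only sample-size justification, and it concerns the outcome the section names as primary. If the figure is off, the risk of missing a true 1.0-point difference is larger than stated, and the calculation cannot be reproduced.

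**Working it through.** **Inputs** (protocol article): difference 1.0 point; SD of change 4.0; two-sided alpha 0.05; stated power 0.90; 1200 randomised 1:1; 50% retention, so 1200 × 0.50 = 600 completers, 300 per arm; ICC 0.31 for baseline scores; effect sizes 0.25 and 0.257.

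**1. The plan's own figure.** For two equal groups of n, the noncentrality is d × √(n/2). With d = 0.25 and n = 300 this is 0.25 × √150 = 3.062.
- Normal approximation: Φ(3.062 − 1.960) = 86.5%.
- Noncentral t: 86.4%.

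The stated 90% is not reproduced.

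**2. The other effect size.** With d = 0.257 the noncentrality is 0.257 × √150 = 3.148. Power is 88.3% (normal) or 88.2% (t). This also falls short of 90%.

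**3. What 90% would require** (noncentral t).

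| Effect | Completers per arm | Total completers | Retention needed of 1200 |
|---|---|---|---|
| 0.25 | 338 | 676 | 56% |
| 0.257 | 320 | 640 | 53% |

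Conversely, with 300 per arm the effect detectable at 90% power is (1.960 + 1.282) × √(2/300) = 0.265. At SD 4.0 that is 0.265 × 4.0 = 1.06 points.

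**4. Alternative readings.** A one-sided 0.05 test gives 92%, which contradicts the two-tailed specification. Taking 600 completers per arm gives 99%, which contradicts 50% retention of 1200. Neither yields 90%.

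**5. Where 0.257 could come from.**
- Without clustering: 1.0/4.0 = 0.250.
- Taking 4.0 as the total SD and removing a between-clinic share of 0.31: 1.0/(4.0 × √(1 − 0.31)) = 1.0/3.32 = 0.301.
- Working backwards: 1.0/0.257 = 3.89, and 1 − (3.89/4.0)² ≈ 0.054. So 0.257 is the within-clinic effect if the change-score ICC is about 0.054.

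The printed SD and ICC do not give 0.257. An unstated ICC of about 0.054 would.

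**6. Sensitivity to the change-score ICC.** The article gives no value, so these are assumptions. 4.0 is taken as the total SD, and the clinic intercept removes the between-clinic share: d = 0.25/√(1 − ICC), 300 per arm, noncentral t.

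| Assumed ICC of change | d | Power |
|---|---|---|
| 0 | 0.250 | 86.4% |
| 0.05 | 0.256 | 88.0% |
| 0.10 | 0.264 | 89.7% |
| 0.15 | 0.271 | 91.2% |

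Power reaches 90% on this basis once the assumed ICC is about 0.11.

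**The case against.** The strongest reply is that 0.257 may be a sound within-clinic effect size. The section says the variance of change has a between-clinic part, and the analysis fits a clinic intercept. A total SD of 4.0 and a within-clinic SD of 3.89 can therefore both be true, and a condensed article may leave the derivation to the full protocol. This stands in part: 0.257 is shown to be underivable from the printed inputs, not to be wrong. It does not rescue the 90%, because 0.257 gives 88.2% and the sentence carrying the claim uses 0.25.

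A second reply is that the gap is small: 3.6 percentage points at 0.25, 1.8 at 0.257, and 0.06 of a point on the knowledge scale. That also stands, and it limits the weight of the finding.

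Two stronger readings are tempting, and the documents do not support either.
- A reader might infer that the trial is underpowered. But patients are randomised individually and the model includes a clinic intercept, so clustering need not cost power and may add some. At an assumed change-score ICC of about 0.11 or more, power reaches 90%. For the same reason, a cluster-trial design effect built from the ICC of 0.31 does not describe this design.
- A reader might infer that clinic effects drop out of change scores, so that no ICC is relevant. The section says the opposite, since it gives change a between-clinic component.

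**Conclusion.** The point holds as an error in a stated figure. On the article's own inputs, 600 completers give 86.4% power at 0.25 and 88.2% at 0.257, so the claim of 90% is wrong as written on either effect size. At 0.25 the type II error is 13.6% where 10% is claimed, before any gain from the clinic intercept. The two effect sizes are unreconciled, and the ICC shown belongs to a different variable from the one powered.

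These figures rest on a two-sample comparison with 300 completers per arm, SD 4.0 and two-sided alpha 0.05, all taken from the article. The power the planned multilevel model would actually have depends on a change-score ICC that is not given; assumed values from 0 to 0.10 put it at about 86% to 90%. The shortfall is modest, and nothing here shows the sample size to be inadequate.

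**What to change.** Rewrite the power statement along these lines: *With 600 completers the trial has about 86% power to detect 1.0 point (SD 4.0, d = 0.25), or 90% power to detect about 1.06 points (d = 0.265), before any gain from the clinic random intercept.*

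Use one effect size throughout the section. If a clustering adjustment is kept, replace the baseline-score ICC with the assumed ICC of the change score, say whether 4.0 is the total or the within-clinic SD, and give the formula for individual randomisation within clinic, so that 0.257 or its replacement can be reproduced.

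The cost is a revision of the power paragraphs. Sample size, randomisation and analysis do not change.

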#### Hypothesis

*Patients earlier in the CKD continuum, patients who speak Spanish, and non-White patients will have less knowledge about the opportunities for and risks and benefits of living kidney donation and will be making less informed LDKT decisions.*

### Aim 2

To conduct a randomized controlled trial in English and Spanish of *ET@Home* for CKD Stage 3–5 patients to assess its effectiveness to increase LDKT knowledge and decision-making by race/ethnicity and primary language spoken as compared to the standard KPSC education.

#### Hypothesis 1

*At the conclusion of the trial, CKD patients who receive ET@Home will have greater transplant knowledge and be more likely to make an informed treatment decision than patients receiving KPSC education alone.*

#### Hypothesis 2

*ET@Home will be more or equally effective for patients earlier in the CKD continuum, patients who speak Spanish, and non-White patients than patients in these subgroups receiving KPSC education alone.*

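### The 90% power claimed for 1-point subgroup differences by interaction tests does not follow from the plan's own inputs, which give about 14% to 30%

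*Protocol article*

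**What the plan says.** The Power analysis section sizes the trial on the transplant knowledge change score. It states that "a mean knowledge change score of 1.0 points is estimated necessary to be detected", describes the variance components as "yielding a pooled standard deviation estimate of 4.0", and adds that "Participant retention will be 50% at the 6-month assessment" and that "Outcomes will be assessed using two-tailed statistical tests" with alpha 0.05. On this basis 600 completers are said to give 90% power for an overall standardized effect of 0.25 (0.257 in the preceding paragraph).

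The section then extends the claim to subgroups. Crediting the stratified recruitment and randomization, it says that "this sample size will also have 90% power to detect 1 point differences in change on the transplant knowledge scale" between the two education conditions "for these critical subgroups using interaction terms (e.g., treatment by race interaction, language by race interaction"). Table 3 gives the numbers randomized: 200 in each of four English-speaking race/ethnicity groups, 400 Spanish-speaking Hispanic patients, and 400 in each CKD stage.

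The Statistical analysis section confirms the test: after the primary analyses, condition-by-subgroup interaction terms are fitted for race, primary language and CKD stage.

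**The concern.** The article gives the same power, 90%, for a 1-point effect in the whole sample and for a 1-point difference in effect between parts of that sample. Both cannot hold. A difference between two subgroup effects carries the sampling error of both, so its standard error is at least twice that of the overall effect at the same SD and total number.

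Aim 2 asks about effectiveness by race/ethnicity and primary language, and the interaction tests are the planned way to compare effects across those groups. A reader who trusts the 90% would give a null interaction far more weight than it can bear. At 14% to 30% power, a true difference as large as the whole planned effect would be missed 70% to 86% of the time.

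**Working it through.** **Inputs.** From the Power analysis section: difference 1.0 point, SD 4.0, two-sided alpha 0.05 (z = 1.96), 50% retention, and "intraclass correlation coefficient (ICC) of 0.31" for baseline knowledge within clinics. From the randomization paragraph: 1:1 allocation, stratified by race/ethnicity, language and CKD stage. From Table 3, halved for retention: 100 completers in each English-speaking race/ethnicity group, 200 Spanish-speaking, 400 English-speaking, 300 Hispanic, 500 non-White, and 200 per CKD stage.

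**The plan's overall figure.** SE = 4 × √(2/300) = 0.327. Power = Φ(1/0.327 − 1.96) = 86.5% at an effect of 0.25. At 0.257 it is 88.3%. So the whole sample comes close to 90% for 1 point but does not reach it.

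**Upper bound for any two-group interaction.** The best case is an even split, 300 against 300: SE = 4 × √(4/300 + 4/300) = 0.653, exactly twice the overall SE. Power = Φ(1/0.653 − 1.96) = Φ(−0.43), about 33%. At SD 4.0 no two-way split of 600 completers does better.

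**Interaction power for 1 point with the Table 3 sizes.** SE = 4 × √(4/n₁ + 4/n₂); power = Φ(1/SE − 1.96) + Φ(−1/SE − 1.96). The detectable difference at 90% power is (1.96 + 1.28) × SE.

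| Contrast | Completers | SE | Power for 1 point | Detectable at 90% |
|---|---|---|---|---|
| English vs Spanish | 400 vs 200 | 0.693 | 30% | 2.2 points |
| Two CKD stages | 200 vs 200 | 0.800 | 24% | 2.6 points |
| White vs non-White | 100 vs 500 | 0.876 | 21% | 2.8 points |
| Two race groups | 100 vs 100 | 1.131 | 14% | 3.7 points |

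Tests over all levels at once do no better. The 3-df race test has 14% power if the White group differs by 1 point and 22% if the Hispanic group does. The 2-df stage test has 18% to 23%.

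**Generous variants, for language (the strongest contrast above).**
- SD 3.89 (= 1/0.257): 32%.
- SD 3.32 (= 4 × √(1 − 0.31), the whole ICC credited as variance removed): 41%.
- SD 4.0 and no attrition: 53%.
- SD 3.32 and no attrition: 69%.

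To reach 90% at 50% retention, the SD would have to be about 1.8 for language or 1.1 for a race pair. At SD 4.0, language would need about 5.04 × 600 = 3,026 completers.

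**The other reading: treatment effect within one subgroup.** SE = 4 × √(4/n).

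| Completers | Example | Power, SD 4.0 | Power, SD 3.32 |
|---|---|---|---|
| 100 | one English-speaking race group | 24% | 33% |
| 200 | Spanish-speaking; one CKD stage | 42% | 57% |
| 300 | all Hispanic | 58% | 74% |
| 400 | English-speaking; CKD 3 and 4 together | 71% | 85% |
| 500 | non-White | 80% | 92% |

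**The case against.** The strongest reply is that the sentence speaks of differences between the two education conditions for the subgroups, so it may mean the treatment effect inside each subgroup. That reading is plausible, and it narrows the gap. Non-White patients reach 80% at SD 4.0 and 92% at SD 3.32, and CKD 3 and 4 together reach 71% and 85%. A reader might infer that power is far below 90% in every subgroup; for the largest groups that is too strong. What stands is that no subgroup reaches 90% at the stated SD and retention, and that Spanish speakers and single race groups stay well short even at the lower SD. The sentence also names interaction terms as the method.

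A reader might also infer that Hypothesis 2 asserts equal effects across subgroups and will be supported by a null interaction. The documents do not say so. The hypothesis that the program "will be more or equally effective for patients earlier in the CKD continuum, patients who speak Spanish, and non-White patients" goes on to name its comparator: members of those same subgroups who get only the health system's standard education. No section commits to reading non-significance as equality. The misreading is a risk, not a stated plan.

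Stratification and multiple imputation do not rescue the figure. Stratification already enters through the Table 3 sizes and balanced arms. Imputation does not restore lost six-month outcomes, and the no-attrition variants show what complete data would give.

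Finally, the heterogeneity models follow the primary analyses, so the error leaves the primary comparison and the enrolment target untouched. That is true and limits the consequence. But the false figure is stated outright and concerns a named aim, so it is not a detail left to a fuller document.

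**Conclusion.** The 90% subgroup power is wrong as stated. The plan's own inputs give roughly a sixth to a third of it for the interaction tests. This rests on equal SD and equal 50% retention across subgroups, 1:1 arms within them, and no further design effect, because the 4.0 is said to contain both variance components and patients are randomized individually. The document gives no SD or retention by subgroup, so the exact percentages are conditional on these assumptions. The conclusion is not sensitive to them: the SD would have to be less than half the stated value for even the language interaction to reach 90%. The point does not show that Hypothesis 2 is badly framed or that the primary analysis is underpowered by design.

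**What to change.** - Delete the 90% subgroup claim from the Power analysis section.
- Replace it with either the actual interaction power for 1 point or the interaction detectable with 90% power, taken from the first table above, with the assumptions stated.
- If a within-subgroup effect was meant, say so and give the power by subgroup size.
- Because Aim 2 and the planned interaction tests address subgroups, present these results as differences in effect with 95% confidence intervals. Note that a non-significant interaction could not support a conclusion of equal effectiveness.

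Hypothesis 2 need not be reworded on this ground. The cost is a less favourable stated figure and a few sentences of text. No patients, visits or analyses are added.

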### Measures

#### Demographic and clinical characteristics

Patient demographics, including patients’ gender, age, race/ethnicity, preferred language, and CKD stage will be obtained from the KPSC electronic medical record.

#### Kidney transplant Derailers index

Measures common transplant derailers such as level of education, health literacy, financial stability, neighborhood/environmental safety, access to transportation, and social support. Health literacy will be assessed with two items measuring subjective health literacy that were shown to detect health literacy as well as gold standard measures such as the S-TOHFLA and the REALM [36].

#### Global Health-related quality of life

Global HRQOL will be measured with the PROMIS 10-item global health scale [37], which produces summary physical and mental scores, each of which has 4 items supported by factor analyses and IRT analyses, with good reliabilities found: physical = 0.81, mental = 0.86.

#### Previous transplant education

The measure of previous transplant education captures the quantity and quality of transplant education, and it has been correlated with taking action toward pursuing transplant in previous studies [26].

#### Small steps

A measure of whether patients took any of 25 steps toward transplant (e.g., “Do you plan to talk through your treatment options with people you trust?” or “Do you plan to call the transplant center to begin evaluation?”). At each survey, patients will be asked whether they had “Already done,” “Plan to do,” or “Don’t plan to do” each step. These questions will be completed at baseline and six months.

#### Level of medical mistrust

Medical Mistrust will be measured with the Medical Mistrust Index (MMI) [38]. This scale was supported by factor analysis and exhibits moderately strong test-retest reliability, with correlation coefficients ranging from 0.3–0.7.

#### LDKT and DDKT self-efficacy

The factor structure for the LDKT scale was verified with exploratory and confirmatory factor analyses, demonstrating a good fit for a one-factor solution (loadings ranging between 0.61–0.91) [32]. The Cronbach’s alpha was 0.88, indicating a high level of internal reliability. The factor structure of the DDKT scale was also verified with exploratory and confirmatory factor analyses, demonstrating a good fit for a one-factor solution (loadings ranging between 0.50–0.73) [39]. The alpha was 0.85, indicating good internal consistency reliability. Self-efficacy will be measured at baseline and six months.

#### CKD, LDKT and DDKT knowledge

A knowledge scale was created using items our team has employed in several previous studies and legacy measures [6, 35, 40] and new questions in response to issues raised by patients and clinicians. A scale created from the extant items has been evidenced with factor analyses [41]. Knowledge will be measured at baseline and six months.

#### Informed decision-making

An informed decision-making measure was created from legacy measures and items generated from our formative work. Items for this scale were selected from legacy scales with good psychometric properties, like the Decisional Conflict Scale, whose total scale and subscales evidence high internal consistency, with Cronbach’s alphas ranging between 0.6–0.9. There was not a statistically significant difference between test-retest scores for this scale, and there was a high correlation (r = 0.80) between them [42]. Informed decision-making will be measured at baseline and six months.

#### Process evaluation

At the six-month follow-up assessment, all intervention participants will complete an evaluation of the helpfulness of and their satisfaction with the print and video materials, text messages, and the *ET@Home* program as a whole.

### Statistical analysis

The available demographic and clinical characteristics of patients who refuse to join the study will be compared to those who enroll to determine if the patient selection procedure has resulted in a biased sample. A similar analysis will be conducted to compare the patients who fail to complete the six-month assessment. Multiple imputation by chained equations (MICE) will be used to multiply impute missing data. Imputation models will include all analysis and stratification variables. The intent-to-treat (ITT) approach will be applied in that all study participants will be analyzed according to the group that they were randomized to, regardless of whether they actually received their assigned intervention or not. Responses to the six-month intervention evaluation will be summarized for the sample overall and by levels of the stratification factors.

It is hypothesized that patients earlier in the CKD continuum, patients who speak Spanish, and non-White patients will have less knowledge about the opportunities for and risks and benefits of living kidney donation and will be making less-informed LDKT decisions. Investigators will evaluate these hypotheses using data from the pre-survey (baseline) by fitting multilevel random effects models with a random intercept to account for clustering at the CKD clinic level to compare differences in knowledge, informed decision-making, and Self-Efficacy. First, unadjusted models will be examined with the race/ethnicity, primary language spoken, and stage of CKD as independent variables for each test (separate models for each). Then, each of these models will be adjusted for other factors hypothesized to impact each outcome, including level of socioeconomic vulnerability, the level of previous transplant education received, the level of medical mistrust, and the level of health literacy. The addition of these variables will help test and control for confounding.

Next, the effectiveness of *ET@Home* for CKD Stage 3–5 patients to increase LDKT knowledge and decision-making compared to KPSC education, by race/ethnicity and primary language spoken, will be evaluated. First, it will be determined if baseline differences in patient- and clinic-level variables are present using χ2 and Wilcoxon rank-sum tests, and subsequently adjustments for any out-of-balance characteristics in outcome analyses will be made. Differences in changes in transplant knowledge and Self-Efficacy using change scores, defined as the difference between the baseline and post-survey assessments, will be examined. Differences in these outcomes between the educational conditions will be tested using multilevel random effects models with normal outcome distributions, accounting for clustering with a random intercept for CKD clinic. Differences in informed decision-making will be examined using multilevel random effects logistic models. Finally, for the number of new steps taken, differences between the educational conditions in the count of new steps will be analyzed with a multilevel random effects Poisson model.

After the primary analyses are completed, multilevel random effects models will be constructed to examine the heterogeneity of treatment effect (HTE) using interaction terms for the *ET@Home* educational condition by the key patient subgroups by which randomization was stratified, including race, primary language spoken, and stage of CKD. For example, the *ET@Home* educational condition (*ET@Home* vs. SOC) x primary language (English vs. Spanish) interaction term will be tested, enabling us to determine of the *ET@Home* intervention was more or less effective for primarily Spanish-speaking patients than English-speaking patients.

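### The stated imputation rule, taken literally as main effects only, does not fit the planned treatment-by-subgroup models and would roughly halve those interactions at 50% retention

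*Protocol article*

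**What the plan says.** All of the following is in the protocol article.

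- **Missing data (Statistical analysis).** "Multiple imputation by chained equations (MICE) will be used to multiply impute missing data". Outcomes are not excepted. The content of the model is given as: "Imputation models will include all analysis and stratification variables". Nothing is said about product terms or about imputing by arm.
- **Analysis set (Statistical analysis).** Intention to treat: "all study participants will be analyzed according to the group that they were randomized to".
- **Expected loss (Power analysis).** "Participant retention will be 50% at the 6-month assessment".
- **Subgroup models (Statistical analysis).** After the primary analyses, multilevel models will "examine the heterogeneity of treatment effect (HTE) using interaction terms" for treatment by race, by primary language and by CKD stage. The language interaction is given as the worked example.
- **Planning values (Power analysis).** For the main comparison, "a mean knowledge change score of 1.0 points is estimated necessary to be detected", with variance components "yielding a pooled standard deviation estimate of 4.0". The same section claims 90% power for 1-point differences in the subgroups by way of interaction terms.

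**The concern.** Multiple imputation gives sound estimates only if the imputation model is at least as rich as the analysis model. Here the analysis model has treatment-by-subgroup products, while the imputation model is described only as a set of variables. The article has its own term for products, interaction terms, and does not use it in the imputation sentence. The literal reading, and the usual default of chained-equations software, is therefore main effects.

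Under that reading, imputed outcomes are generated as if ET@Home had the same effect in every race, language and stage group. With about half of the six-month outcomes imputed, this built-in homogeneity is averaged with the real data. The affected analyses are not incidental. Aim 2 asks about effectiveness by race/ethnicity and language, small groups are oversampled, and randomisation is stratified by the same factors.

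**Working it through.** **1. The plan's own figure.** With 600 completers (300 per arm) and two-sided 0.05, power = Φ(d·√(300/2) − 1.96).

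- d = 0.257: Φ(3.148 − 1.96) = 0.88, close to the stated 90%.
- d = 0.25: Φ(3.062 − 1.96) = 0.86.

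This concerns the main comparison and does not depend on the imputation model.

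**2. Reference power for the language interaction.** Table 3 has 400 Spanish-speaking and 800 English-speaking patients. At 50% retention, 200 and 400 are observed, split 1:1 by arm. With SD 4.0:

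- SE = 4·√(4/200 + 4/400) = 0.693.
- Power for a 1.0-point interaction = Φ(1/0.693 − 1.96) = Φ(−0.517) = 0.30.

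So about 30% is what a correctly specified analysis can reach, not the claimed 90%. That shortfall is a separate matter. The 30% serves here only as the benchmark.

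**3. Expected attenuation under main-effects imputation.** Let r be retention, δ the true interaction and P the pooled treatment effect. In each subgroup the completed-data effect is r × (subgroup effect) + (1 − r) × P. With equal retention the P terms cancel in the difference between subgroups, which leaves r × δ. For δ = 1.0 this gives 0.50 at r = 0.50, 0.75 at r = 0.75 and 0.90 at r = 0.90.

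**4. Simulation.** There were 1200 patients in the Table 3 layout and 1:1 allocation within strata. Change SD was about 4, and the arm effect was 1.0 in English speakers. Analysis used Rubin's rules with 20 imputations (10 for predictive mean matching) and 100 to 800 runs per row. Assumptions not taken from the article: a baseline-to-change slope of −0.3, missingness unrelated to outcome, and no clinic random effect. The true treatment-by-language interaction is 1.0.

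| Imputation model | Retention | Mean estimate | Spread of estimates | Mean Rubin SE | Rejection rate |
|---|---|---|---|---|---|
| Main effects only | 50% | 0.50 | 0.37 | 0.60 | 3.8% |
| Main effects, predictive mean matching | 50% | 0.49 | 0.36 | 0.60 | 2.0% |
| Treatment-by-language term added | 50% | 1.01 | 0.69 | 0.69 | 31% |
| All treatment-by-stratum terms added | 50% | 1.02 | 0.66 | 0.69 | 31% |
| Separately by arm | 50% | 0.99 | 0.68 | 0.69 | 30% |
| Main effects only | 75% | 0.73 | 0.42 | 0.55 | 22.5% |
| Main effects only | 90% | 0.89 | 0.47 | 0.51 | 40% |

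Complete cases at 50% retention gave a mean of about 1.0 and rejection of about 30%, in line with step 2.

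**5. Why power falls so far.** Two things combine. The estimate is halved, and the Rubin SE (0.60) is much larger than the actual spread (0.37) because the two models conflict. Significance needs an estimate above 1.96 × 0.60 = 1.18, while the estimates centre on 0.50. With no true interaction the test rejects in 0.2% of runs instead of 5%.

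**6. Sensitivity.** A true interaction of 2.0 is estimated at 0.98. Retention of 55% and 45% in the two arms gives 0.49. If Spanish speakers retain 35% and the others 50%, the estimate falls to 0.38.

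**7. Subgroup and overall effects.** Suppose the true effect is 1.5 points in English speakers and 0 in Spanish speakers, with equal 50% retention.

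- Pooled effect: (800 × 1.5 + 400 × 0)/1200 = 1.0.
- English estimate after imputation: 0.5 × 1.5 + 0.5 × 1.0 = 1.25.
- Spanish estimate after imputation: 0.5 × 0 + 0.5 × 1.0 = 0.5.
- Overall estimate: (800 × 1.25 + 400 × 0.5)/1200 = 1.0, unchanged.

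The distortion lies in the subgroup contrasts, not in the overall effect.

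**The case against.** The strongest reply is that the article does not prescribe a main-effects model. Product terms belong to the planned analysis models, so a careful analyst could count them among the analysis variables, and then there is no bias. This stands, and it makes the point conditional. It does not remove it: the article does state a rule for the imputation model, and a literal implementation of that rule satisfies the text and gives a wrong answer to a central question.

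A second reply is that imputation detail belongs in an analysis plan that is not shown. That is fair for software settings or the number of imputations. Here the content of the model is itself stated, in a form that allows the faulty version.

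Third, the heterogeneity analyses follow the primary ones, 50% is only a planning figure, and power would be low even with correct imputation. All true. They limit the weight of the point, but low power is no reason to halve the estimate as well.

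Two stronger readings are tempting and not supported.

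- A reader might infer that the plan confirms Hypothesis 2 by construction, since shrunken interactions look like equal effectiveness. As worded, Hypothesis 2 compares ET@Home recipients with control patients in the same subgroups, not with other subgroups. Attenuation would also hide a larger benefit in a subgroup, and a non-significant interaction does not establish equality.
- A reader might infer that heavy loss in an unblinded trial makes a delta-adjusted analysis a necessary correction here. That is a separate question about the missing-data mechanism. Nothing calculated here bears on it, and the unseen analysis plan may already contain such an analysis.

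**Conclusion.** The point holds in conditional form. The imputation sentence permits a main-effects model, and such a model is not compatible with the treatment-by-race, treatment-by-language and treatment-by-stage analyses. At the planned 50% retention it would shrink a true 1.0-point interaction to about 0.5 and cut the power of the language test from about 30% to about 4%. The size follows retention (about 0.73 at 75%, 0.89 at 90%), and the problem vanishes if the product terms are included or imputation is done by arm (0.99 to 1.02).

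The figures are for the knowledge change score. They assume missingness unrelated to outcome, SD about 4 and no clinic random effect. Only the language interaction was simulated. The same mechanism applies in kind to the race and stage interactions. The main comparison between arms is not shown to be affected. The change should be made, because it costs almost nothing and protects analyses for which recruitment and randomisation were stratified.

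**What to change.** Amend the imputation sentence in Statistical analysis in one of two ways:

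- **By arm.** Impute six-month outcomes separately within each randomised arm, with the race/ethnicity-language group, CKD stage, baseline scores and clinic in each model. This preserves every treatment-by-covariate term without listing them.
- **By explicit terms.** Keep one imputation model, and state that it includes the treatment-by-race/ethnicity, treatment-by-language and treatment-by-stage terms along with the variables already named.

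The cost is a few lines of imputation code. Imputations become slightly noisier, since each arm-specific model rests on about 300 observed patients (600 completers over two arms). The wider spread of the interaction estimate (about 0.68 against 0.37) is not a real loss of precision: it matches the complete-case spread, and the smaller figure comes from imposing a common effect on half of the data. The change does not bring interaction power near the claimed 90%. That needs separate attention.
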